Currently, there are only two available drugs to treat CD: nifurtimox and benznidazole (BNZ). Of these two, BNZ is the one most studied and most often used as a treatment. However, current schemes of this treatment have some limitations. On the one hand, it has a limited efficacy based on seroconversion (around 50–80% in the acute phase of the disease and 8–20% in the chronic phase) [7]. Another important limitation is the high rate of adverse events (AEs) when using these drugs. The incidence of AEs related to BNZ varies from 40–50% up to 98%, and around 15% of these patients have to definitively stop the treatment for this reason, with the rate even higher in patients treated with nifurtimox [8–10]. The most commonly observed AEs are hypersensitivity (rash, fever, generalized edema, lymphadenopathy, myalgia, and arthralgia), gastrointestinal disorders, bone marrow toxicity (neutropenia and thrombocytopenic purpura), and peripheral polyneuropathy [9]. Current knowledge about the BNZ toxicity mechanisms is scarce because the main studies have focused on the clinical aspects of these AEs [10]. Our group recently carried out an analysis of the cytokine profile and human leukocyte antigen (HLA) classes I and II of patients who were treated with BNZ, and we found a higher treatment discontinuation rate due to skin hypersensitivity AEs in patients who had the HLA-B*3505 allele [11].

Moreover, another drawback of the studies assessing the efficacy of BNZ in chronic CD is the lack of a biomarker to define the cure of disease. Currently, the cure criteria are negative seroconversion of two serologic assays against different antigens, but it usually takes several years after an effective treatment, precluding its use in clinical trials. In addition, detection of *T. cruzi* DNA in peripheral blood cannot be used to define cure, because a negative result does not mean absence of the infection; however, in recent years, it has become an important tool used to identify therapeutic failure when the result remains positive after completed treatment [8].

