• Having laboratory parameters outside the range of normal or that are considered clinically relevant by the responsible physician: ◦ Total leukocyte count must be within the normal range, with an acceptable range of ± 5%. ◦ Total platelet count must be within the normal range up to 550,000/mm^3^ or 550 × 10^9^/L. ◦ Total bilirubin must be within the normal range. ◦ Transaminase levels must be within the normal range, with an acceptable range of 25% above the upper limit of normal (ULN). ◦ Total creatinine level must be within the normal range, with an acceptable variation of 10% above the ULN. ◦ Alkaline phosphatase level must be within the normal range up to < 2.5× ULN. ◦ Gamma glutamyl transferase level must be within the normal range up to 2× ULN. ◦ Fasting glucose must be within the normal range.	

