### Sample size and data analysis

For the sample size calculation, we considered a superiority design for two-sample comparison of proportions. We hypothesize a reduction of 50% of the total number of patients who either have a positive PCR result during follow-up or have to discontinue the treatment due to AEs, has been taken into account as a hypothesis. It is estimated that in the standard arm of treatment, 40% of patients will be evaluated as treatment failures according to the intention-to-treat principle.

Given the expected proportions in every group and given that we plan two pairwise comparisons for a power of 80% and a type I error of 0.05, the total number of patients that should be included in the study is 240, which will comprise 60 participants per country.

The categorical data will be presented as absolute numbers and proportions, and the continuous variables will be expressed as means and standard deviations when normal distribution is demonstrated (using the Kolmogorov-Smirnov test) or as medians and interquartile ranges when it is not.

For comparison of the distribution of categorical variables, the χ^2^ test or Fisher’s exact test will be used, and the Mann-Whitney *U* test or Student’s *t* test will be used for continuous variables, respectively, depending on the presence or not of normal distribution.

A comparative analysis of the main clinicoepidemiological variable among the three groups will be carried out. The primary efficacy analysis will be the comparison of the proportion of patients with sustained parasitologic clearance of each treatment arm compared with the standard arm of treatment. The time until the first positive PCR result for *T. cruzi* will be evaluated by Kaplan-Meier survival analysis with the log-rank test for significance.

The proportion of patients with SAEs and/or AEs leading to treatment discontinuation will be described per trial arm and by System Organ Class (using preferred terms defined by MedDRA 13.1), according to the National Cancer Institute’s Common Terminology Criteria for Adverse Events (version 4.03). Incidence rate and 95% confidence interval will be presented per trial arm for SAEs and AEs per category, along with the most frequent AEs.

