Safety laboratory parameters (hematology and biochemistry) will also be described individually per trial arm, showing the proportion of patients by degree of elevation relative to upper limit of normal and baseline values, as well as blood level changes over time.

Safety data will be correlated to efficacy and treatment compliance data and to PK parameters. Differences in the rate of absorption in serology will be estimated with *t* test pairs or the Wilcoxon test, depending on their distribution. All safety analyses will be carried out on all patients treated, understood as all patients who receive at least one dose of treatment. Finally, the sensitivity, specificity, and positive and negative predictive values of the presence of HLA-B*3505 and their relationship with the occurrence of SAEs will be calculated.

The efficacy analysis will be carried out according to the intention-to-treat principle. The group of patients analyzed will be all randomized patients in each of the treatment branches. Cases lost during follow-up and dropouts will be considered treatment failures.In addition, a per-protocol analysis will be defined as all patients receiving randomized treatment who meet the main criteria, have not permanently left the administration of the treatment, and have no other protocol deviation. Patients lost to follow-up will be excluded unless they present a positive PCR result, in which case, they will be included in the analysis. The results will be analyzed using IBM SPSS Statistics version 19.0 software (IBM Corp., Armonk, NY, USA).

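### The categorical laboratory summary grades hematology only by elevation, so it has no category for the low counts that the protocol names as a benznidazole toxicity

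*Protocol article*

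**What the plan says.** Three parts of the protocol article bear on this.

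- **Laboratory summary (Sample size and data analysis).** The scope is stated outright: "Safety laboratory parameters (hematology and biochemistry) will also be described individually per trial arm". The categorical rule for that whole scope is "showing the proportion of patients by degree of elevation relative to upper limit of normal and baseline values". The sentence then adds a second display, "as well as blood level changes over time".
- **Known toxicity (Introduction).** The list of the drug's commonest adverse events includes "bone marrow toxicity (neutropenia and thrombocytopenic purpura".
- **Adverse event reporting (Sample size and data analysis).** A separate paragraph refers to the "Common Terminology Criteria for Adverse Events (version 4.03" and plans a further display: "Incidence rate and 95% confidence interval will be presented per trial arm for SAEs and AEs per category". The section on SAEs and unblinding requires all adverse events to be reported.

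Table 3 schedules hematology at the selection visit, at days 7, 15, 28 and 60, and at unscheduled side effect visits.

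**The concern.** Grading by elevation suits transaminases, bilirubin and creatinine, where toxicity shows as a rise. It points the wrong way for blood counts, because the hematological toxicity that the protocol itself names is a fall. Following the sentence as written, an analyst would produce a hematology table of proportions that cannot register neutropenia or thrombocytopenia.

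At stake is one component of the safety comparison. Tolerability and safety of the regimens is a secondary objective, the article lists adverse event incidence and severity under its primary endpoints, and the trial is meant to identify the most suitable regimen on efficacy and safety together. A per-arm count of patients with low values, taken from the measured counts, would inform that comparison without depending on whether an investigator recorded each low value as an adverse event. As written, the plan states no such count.

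**Working it through.** No arithmetic applies: the point turns on the direction of a classification rule, not on sample size, power or event counts. The article gives no figure to reproduce.

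**Step 1: scope.** The laboratory sentence names hematology and biochemistry together and gives them a single categorical rule. Nothing elsewhere in the article sets a different rule for blood counts.

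**Step 2: direction.** The rule has two reference points, the upper limit of normal (ULN) and the baseline value, and the word elevation governs both. The lower limit of normal (LLN) does not appear in the rule, nor does any degree of decrease.

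**Step 3: apply the rule to a falling count.** Let x be the post-baseline count and b the baseline count, with x < b and x < LLN.

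- Against the ULN: x < LLN < ULN, so x is not elevated.
- Against baseline: x < b, so x is not elevated.

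Both tests give the same answer however deep the fall. Two invented records show it:

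| Record | Baseline | On treatment | Category under the stated rule |
|---|---|---|---|
| Neutrophils (×10⁹/L) | 4.0 | 0.8 | No elevation |
| Platelets (×10⁹/L) | 250 | 40 | No elevation |

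**Step 4: compare with the named toxicity.** Neutropenia and thrombocytopenic purpura both present as low counts, so both belong to the case in step 3.

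**Step 5: compare with the entry criteria.** Table 2 begins its leukocyte criterion "Total leukocyte count must be within the normal range" and allows a 5% tolerance either way. It also requires platelets within the normal range, extending only the upper end. The protocol thus treats low leukocytes and platelets as relevant when patients enter, but the on-treatment proportions do not count them. Table 2 sets no limit for neutrophils or hemoglobin, so this comparison covers leukocytes and platelets only.

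**Step 6: look for another count.** The display of changes over time has no stated format. If it follows the article's general rule for continuous variables (mean and standard deviation, or median and interquartile range), a few deep falls within an arm of 240 / 3 = 80 patients could be hard to see, and no patient would be classified as low. The adverse event tables count reported events. The article does not say that every low count must be recorded as an adverse event.

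**The case against.** The strongest reply is that marrow toxicity has other routes into the report. The same sentence plans a display of changes over time, where falling counts could show. The protocol treats neutropenia and thrombocytopenic purpura as adverse events, requires all adverse events to be reported, and plans incidence with 95% confidence intervals per arm. That incidence display is not restricted to serious or treatment-stopping events. Hematology is drawn at the treatment visits where adverse events are also recorded. All of this stands, and it limits the consequence.

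A reader might therefore infer too much in three ways:

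- **That the safety report would show no marrow signal in any arm, whatever the true rate.** The text does not support this. It is true only of the proportions graded by elevation.
- **That reactive rises in leukocytes would be counted as toxicity.** The article describes proportions by degree of elevation. It does not label a rise as toxicity, and it ties no test or decision to this table.
- **That a definite number of patients would be missed.** Any such number needs a cytopenia rate, and the article gives none.

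A further reply is that a journal article condenses the full protocol, that laboratory table layouts usually belong in the analysis plan, and that the wording may be shorthand written with liver enzymes in mind. This lowers confidence about what would finally be tabulated. It does not remove the point, because the sentence names hematology and states a direction. That is a rule fixed badly, not a detail left for later.

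**Conclusion.** The point holds for the categorical laboratory summary. As written, that summary has no category for low hematology values, so it cannot count patients with the marrow toxicity that the Introduction names. The other two displays may reveal such patients, but neither is stated to give a per-arm count of them from the measured values.

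Within that table the gap is complete by definition and needs no assumed event rate. Its effect on the overall safety evaluation is modest: the table is descriptive, adverse event reporting is a separate route, and the measurements are taken in any case, so the count can be recovered. The conclusion assumes that the sentence is applied literally and that no fuller document already grades hematology in both directions. The change is worth making because it is cheap and lets the laboratory comparison register the named toxicity.

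**What to change.** Split the sentence by type of parameter.

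- **Biochemistry** (transaminases, bilirubin, alkaline phosphatase, gamma glutamyl transferase, creatinine): keep the proportions by elevation against the ULN and baseline.
- **Hematology** (leukocytes, neutrophils, platelets, hemoglobin): report the proportion of patients per arm by worst post-baseline decrease, both below the LLN and from baseline, using the CTCAE version 4.03 grades already adopted for adverse events. Use the article's existing safety population, all patients who received at least one dose.

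State also that baseline for hematology is the selection visit value, since Table 3 shows no hematology on day 0.

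The cost is one sentence of analysis wording and one extra table. No new sampling is needed, assuming that the scheduled hemogram reports neutrophils, platelets and hemoglobin; the article does not list its components.

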#### Primary endpoints

The primary endpoint is parasitologic response, defined as maintained negative qualitative PCR results during the 12-month follow-up period. For efficacy assessments, the end of treatment of each treatment arm will be defined in accordance with the duration of the treatment regimen. Incidence and severity of AEs and those leading to treatment discontinuation will also be recorded.

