**Recruitment sites**

Countries involved in the recruitment will be Spain (University Hospital Vall d’Hebron, Barcelona; University Hospital Ramón y Cajal, Madrid), Argentina (Instituto Nacional de Parasitología [name] Chaben, Buenos Aires; Instituto de Cardiología Juana Francisca Cabral, Corrientes), Brazil (Centro de Pesquisas René Rachou – Fundação Oswaldo Cruz, Belo Horizonte; Hospital Universitário Clemente de Faria, Montes Claros), and Colombia (Fundación Cardioinfantil – Instituto de Cardiología).
2.**Selection phase**

Patients with CD in the chronic phase who come to the study centers will be evaluated in order to assess if they meet the inclusion criteria. For those who agree to participate and sign the informed consent, detection of parasitic DNA by PCR in peripheral blood will be performed. Patients with a PCR result negative for *T. cruzi* will be withdrawn from the study. The screening procedure must occur up to 90 days or less before the initiation of treatment. Serology and DNA determination by PCR will be accepted as valid and will not need to be repeated if a positive result was obtained in a previous period of 3 months.

All patients will undergo a clinical history and physical examination. Peripheral blood extraction will be performed for analysis: hemogram, biochemistry assays, and HLA study, and a negative pregnancy test (either in urine or blood) is mandatory in case of women in childbearing age. The evaluation of the visceral involvement of CD will be completed with a chest x-ray and electrocardiogram. The performance of other complementary tests will be carried out according to the clinical investigator’s decision, but they will not be considered necessary for the inclusion of the patient.
3.**Treatment phase**

In this phase, the patient will be randomized to one of the three arms of treatment, whose duration will be 60 days independently of the arm assigned. Initially, a baseline visit will be performed in which the patient will be trained on how to take the drug and identify AEs. After that, a total of four scheduled visits will occur during the treatment period, at 7, 15, 28, and 60 days after treatment initiation. A summary of these visits is presented in Table 3.

**Table 3 Tab3:** Visit schedule

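### The per-protocol rule keeps a lost patient only if a PCR was positive, so membership of the set depends on the outcome and its failure proportion can be inflated

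*Protocol article*

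**What the plan says.** Under Sample size and data analysis, the protocol article makes intention-to-treat the efficacy analysis: "The efficacy analysis will be carried out according to the intention-to-treat principle". It covers all randomized patients, and "Cases lost during follow-up and dropouts will be considered treatment failures".

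The same section adds a per-protocol analysis. Patients must have received their randomized treatment, met the main criteria, and "have not permanently left the administration of the treatment, and have no other protocol deviation". For losses it says "Patients lost to follow-up will be excluded unless they present a positive PCR result, in which case, they will be included in the analysis".

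The endpoint to which this applies, under Primary endpoints, is "maintained negative qualitative PCR results during the 12-month follow-up period".

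Two statements bear on what counts as leaving treatment. Primary endpoints says that, for efficacy assessments, "the end of treatment of each treatment arm will be defined in accordance with the duration of the treatment regimen". The treatment phase under Study organization describes treatment "whose duration will be 60 days independently of the arm assigned", and the follow-up phase there puts the end of the therapeutic scheme at day 60.

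Sample size and data analysis also plans a Kaplan-Meier analysis with a log-rank test for time to the first positive PCR.

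**The concern.** A patient's failure is settled by one positive PCR, but success is settled only at month 12. A patient who is lost early can therefore be a known failure but never a known success. The rule keeps the first kind and discards those still negative when last seen, so membership of the per-protocol set is decided by the result being analysed.

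A reader would naturally use the per-protocol proportion to see whether counting every loss as a failure drives the intention-to-treat result. If the per-protocol proportion itself moves upward with loss, it is a weaker check than it appears, and unequal loss can create a difference between arms that do not differ.

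A second, smaller matter concerns the same set. Whether a patient in the 15-day arm has left treatment depends on which account of treatment duration is applied, so the set in that arm is not fixed by the text.

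**Working it through.** **The plan's own figure.** The article states that "40% of patients will be evaluated as treatment failures according to the intention-to-treat principle" in the standard arm, and hypothesizes a 50% reduction, so 20% in an experimental arm. With 80% power, two-sided 5% type I error (sidedness is not stated) and no continuity correction, the pooled-variance formula gives 82 per arm, or 246 in total. The unpooled formula gives 79 per arm, or 237. Both are within 3% of the stated 240 (80 per arm). The sample size is not in dispute; this only confirms the 40% and 20% inputs.

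**Inputs to the check.**
- p, true failure: 40%, taken from the sample size text as a benchmark. That figure already counts losses and discontinuations as failures, so a pure PCR failure rate may be lower; 20% is shown as well.
- d, proportion lost among patients who would otherwise qualify: not given. Assumed 5% and 20%.
- q, share of lost patients with a positive PCR that counts as failure before loss: not given. If loss is unrelated to outcome, q lies between 0 (none seen in time) and p (all seen in time).

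**Formula.** Completers contribute (1 − d)p failures out of (1 − d). Lost patients contribute dq failures out of dq. So

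per-protocol failure = [(1 − d)p + dq] / [(1 − d) + dq],

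and the excess over p is dq(1 − p) / [(1 − d) + dq]. This is never negative: compared with excluding all lost patients, the rule adds the same count to numerator and denominator.

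**Results at p = 40%.**

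| Loss | q = 0 | q = 0.20 | q = 0.40 |
|---|---|---|---|
| 5% | 40.0% | 0.39/0.96 = 40.6% | 0.40/0.97 = 41.2% |
| 20% | 40.0% | 0.36/0.84 = 42.9% | 0.40/0.88 = 45.5% |
| Gap between two equal arms (unrounded values) | 0 | 2.2 points | 4.2 points |

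In a simulation of 100,000 trials with 80 randomized per arm, equal true failure of 40% and losses of 5% and 20%, a nominal two-sided 5% test on this set rejected 6.0% of the time at q = 0.20 and 8.1% at q = 0.40.

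**At p = 20%** with q at its maximum of 0.20, 20% loss gives 0.20/0.84 = 23.8% and 5% loss gives 0.20/0.96 = 20.8%, a gap of 3.0 points.

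**Intention-to-treat for comparison**, with every loss a failure, (1 − d)p + d at p = 40%: 5% loss gives 43% and 20% loss gives 52%, a gap of 9 points.

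**Where the direction fails.**
- No positive seen before loss (q = 0): no inflation at any loss.
- Unequal true failure, all positives seen before loss: a 40% arm losing 10% gives 0.40/0.94 = 42.6% (up 2.6 points), while a 20% arm losing 12% gives 0.20/0.904 = 22.1% (up 2.1). The arm that loses more is inflated less.
- Informative loss: with 20% lost, completers failing at 40%, lost patients truly failing at 80% and half of those failures seen, true failure is 0.32 + 0.16 = 48.0%, but the rule gives (0.32 + 0.08)/0.88 = 45.5%. Failure is understated.

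**The case against.** Several points on the other side stand.

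- Counting a documented positive as a failure is reasonable, because under this endpoint it is one. The fault is only that the matching lost negatives are dropped.
- The rule touches an additional analysis. The intention-to-treat analysis keeps everyone and does not use it.
- A reader might infer that the per-protocol set is the only check on counting losses as failures. It is not: the planned Kaplan-Meier analysis can keep lost negatives as censored. The article does not give its population or censoring, which an article may leave to the full plan.
- A reader might also infer that agreement between the two analyses is built in because both move upward with loss. The figures do not support that. With equal arms and 5% versus 20% loss, the false gap is 9 points under intention-to-treat and 0 to 4.2 under the per-protocol rule. A difference driven purely by loss would shrink by more than half, so the per-protocol result keeps some diagnostic value.
- Nothing in the article predicts unequal loss in this double-blind trial; 5% versus 20% is illustrative.
- It is tempting to say that a 15-day-arm patient who stops at day 20 is excluded despite having had the whole assigned regimen. The 60-day wording under Study organization points that way, but Primary endpoints ties end of treatment to regimen duration for efficacy assessments. That is an ambiguity, not a settled exclusion.

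None of this removes the selection on outcome, which is in the stated rule and would not be cured by further detail elsewhere.

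**Conclusion.** The point holds in a limited form and should be corrected. As written, the rule selects lost patients into the per-protocol set by their outcome. If loss is unrelated to outcome and some positives are seen before loss, per-protocol failure is overstated: at 40% true failure, by up to 5.5 points with 20% loss and up to 1.2 points with 5% loss, giving a false gap of 0 to about 4 points between equal arms. The loss rates and the share positive before loss are assumptions.

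A reader might conclude that failure is inflated in whichever arm loses more patients. That needs non-informative loss, some positives seen before loss, and similar true failure and detection across arms. The article guarantees none of these, and the counterexamples above show the ordering or the sign can change. Nor is the intention-to-treat comparison biased by this rule.

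The two accounts of treatment duration are a separate inconsistency that leaves per-protocol membership open in the 15-day arm.

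**What to change.** Define the per-protocol set without reference to any PCR result, and keep every patient who meets the treatment criteria, lost or not. Estimate 12-month failure in that set by the Kaplan-Meier method already planned, counting documented post-treatment positives as failures and censoring lost patients at their last negative PCR. Say which PCR visits count, since every patient is PCR-positive at entry and PCR is also done during treatment.

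Separately, reconcile the definition of end of treatment under Primary endpoints with the 60-day statements under Study organization, so that treatment completion for this set is judged the same way throughout.

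The cost is about a paragraph of analysis wording, agreed before unblinding, with no new data. The downside is that censoring assumes loss is non-informative within each arm.

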### Patient eligibility

Patients aged ≥ 18 years having any combination of at least two positive serologic test results against *T. cruzi* (indirect immunofluorescence, indirect hemagglutination, or ELISA) and not having previously received treatment with BNZ or nifurtimox (either completely or partially) will be eligible. Inclusion and exclusion criteria are summarized in Tables 1 and 2, respectively.

**Table 1 Tab1:** Inclusion criteria

Inclusion criteria (patients should meet all criteria)	
• Adults ≥ 18 years old	
• Have been diagnosed with Chagas disease by two positive serological tests using different antigens	
• Have detectable *Trypanosoma cruzi* DNA in peripheral blood through a qualitative interpretation of the polymerase chain reaction technique	
• Written informed consent provided	
• Weight ≥ 50 kg and ≤ 80 kg	
• Ability to comply with all tests and specified protocol visits and have a permanent address	
• Patients must be residents of areas free of vector transmission (*Triatoma infestans*), defined by local health programs or by the Pan American Health Organization/World Health Organization definition.	
• Women of childbearing age should have a urine or serum negative pregnancy test at the moment of the baseline visit. Breastfeeding should not be allowed, and a barrier method of contraception should be used during the treatment phase.

**Table 2 Tab2:** Exclusion criteria

Exclusion criteria	
• Having previously received treatment with benznidazole or nifurtimox (either completely or incompletely)	
• Signs and/or symptoms of severe cardiac form of Chagas disease (as confirmed by local national guidelines)	
• Impossibility to complete the specified protocol follow-up visits	
• Acute or chronic health problems that, in the opinion of the principal investigator, may interfere with the evaluation of the efficacy and/or safety related to the drug (for example, acute infections, human immunodeficiency virus infection, liver or kidney disease)	
• History of alcohol abuse	
• Known hypersensitivity to metronidazole drugs	
• Concomitant use or history of use of allopurinol, antimicrobial, antiparasitic, or antifungal agents	

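### The per-protocol set keeps patients lost to follow-up only if they had a positive PCR, so membership depends on the outcome and the failure rate is biased upward when loss is unrelated to response

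*Protocol article*

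**What the plan says.** All references are to the protocol article; no separate analysis plan is at hand.

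- **Endpoint** (Primary endpoints): parasitologic response is "maintained negative qualitative PCR results during the 12-month follow-up period". One positive PCR after treatment settles failure early; success is known only with complete follow-up.
- **Intention-to-treat analysis** (Sample size and data analysis): all randomized patients are analysed. "Cases lost during follow-up and dropouts will be considered treatment failures".
- **Per-protocol set** (same section): patients who received the randomized treatment, met the main criteria, "have not permanently left the administration of the treatment, and have no other protocol deviation". On losses it adds: "Patients lost to follow-up will be excluded unless they present a positive PCR result, in which case, they will be included in the analysis".
- **Time to first positive PCR** (same section): this "will be evaluated by Kaplan-Meier survival analysis with the log-rank test for significance". The article does not say on which analysis set.

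Nothing in the article offsets the rule on losses by weighting, by a minimum follow-up applied to positives and negatives alike, or by confining the per-protocol analysis to a time-to-event method.

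**The concern.** An analysis set should be defined by things other than the outcome being compared. Here, two patients lost at the same visit are handled differently according to their PCR results: the positive one counts in numerator and denominator, the negative one in neither. Even if losses have nothing to do with response, the failure proportion is pushed up, and by different amounts when arms lose different numbers of patients.

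What is at stake is a supplementary result. Readers will look to the per-protocol analysis to see how far the intention-to-treat result depends on scoring losses as failures. Under the stated rule it still carries part of that loss-driven penalty.

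**Working it through.** **Inputs from the article.** 240 patients randomized 1:1:1, so 80 per arm. The design assumes that "in the standard arm of treatment, 40% of patients will be evaluated as treatment failures" and, as effect, "We hypothesize a reduction of 50% of the total number of patients" who fail, that is 40% v 20%. As a check on these inputs, two-sided 5% and 80% power give 82 per arm (246 in total) with the pooled formula and 79 per arm (237) with the unpooled one, both within 3% of 240. The article states no expected loss rate, so there is no plan figure for the bias itself to reproduce.

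**Assumed inputs.** p = true 12-month failure rate, the same in completers and lost patients (30%, with the design rates as a check); d = share lost; q = share of lost patients' failures already seen as a positive PCR before loss (0.5 to 0.8). The per-protocol result is taken to be a proportion, like the primary comparison.

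**Step 1, direction.** Let completers number n with a failures. Adding x lost failures gives (a + x)/(n + x), which exceeds a/n whenever x > 0 and a < n. So the rate always rises above the completers' rate.

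**Step 2, size.**

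Per-protocol failure = [(1 − d)p + dpq] / [(1 − d) + dpq]

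Bias = p(1 − p)dq / (1 − d + pdq)

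The bias is positive whenever d and q exceed 0 and 0 < p < 1, and it grows with d.

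In patients, with 80 in an arm, 20% lost and p = 30%: 64 completers have 19.2 failures, and 16 lost patients have 4.8. With q = 0.5, 2.4 of these enter: (19.2 + 2.4)/(64 + 2.4) = 32.5%. With q = 0.8, 3.84 enter: 23.04/67.84 = 34.0%.

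| Share lost | p = 30%, q = 0.5 | p = 30%, q = 0.8 |
|---|---|---|
| 5% | 30.6% | 30.9% |
| 10% | 31.2% | 31.8% |
| 15% | 31.8% | 32.8% |
| 20% | 32.5% | 34.0% |
| 25% | 33.3% | 35.2% |

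At the design rates with 20% lost, a true 40% becomes 42.9% (q = 0.5) to 45.5% (q = 1), and a true 20% becomes 22.0% to 23.8%.

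**Step 3, spurious difference between two arms that are truly equal (p = 30%).**

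| Losses | Gap, q = 0.5 | Gap, q = 0.8 | Two-sided 5% test rejects |
|---|---|---|---|
| 10% v 5% | 0.6 points | 1.0 points | about 5% |
| 15% v 5% | 1.3 points | 2.0 points | 5% to 6% |
| 25% v 5% | 2.8 points | 4.3 points | about 7% to 8.5% |

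Rejection rates are simulated with 80 per arm; with no losses the same test rejects about 5%. Equal losses with equal failure rates produce no spurious gap.

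**Step 4, the intention-to-treat rule in the same scenario.** With every loss scored as failure, the rate is p + (1 − p)d. At 25% v 5% lost this is 30% + 70% × 25% = 47.5% against 30% + 70% × 5% = 33.5%, a gap of 14 points, with rejection in about 42% to 43% of simulated trials.

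**Step 5, where the general statements stop holding.**

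- *Informative loss.* If completers fail at 35%, lost patients at 60%, 10% are lost and q = 0.25, the rule gives (0.315 + 0.015)/(0.900 + 0.015) = 36.1%. That is above the completers' 35.0% but below the true 0.9 × 35% + 0.1 × 60% = 37.5%.
- *Different failure rates.* At 40% v 20% with q = 1 and losses of 10% v 12%, the biases are +2.6 and +2.1 points, so the arm with fewer losses has the larger bias.

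**The case against.** The best defence is that a positive PCR settles the matter: the patient has failed, so discarding that patient throws away a known outcome. That is true of the single patient. In a simple proportion, however, keeping observed failures while dropping equally observed negatives is what creates the bias.

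Several stronger readings are tempting, and the article does not support them.

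- *That the per-protocol analysis is the only check on the intention-to-treat rule.* A Kaplan-Meier analysis of time to first positive PCR is also planned, and it can use partial follow-up.
- *That agreement between the two analyses would be false reassurance.* In the 25% v 5% scenario the intention-to-treat gap is 14 points and the per-protocol gap 2.8 to 4.3. The two would usually differ visibly, so the per-protocol result still exposes most of the artefact.
- *That the bias always runs upward and is always largest in the arm with most losses.* Step 5 shows that both statements need conditions.
- *That regimens differ in tolerability and so losses will be unequal.* Patients who permanently stop treatment are already outside the set under another clause, and the article does not establish that tolerability differs: its Discussion argues that a higher dose need not bring more adverse events.
- *That a positive PCR at entry or during treatment could bring a lost patient in.* Every patient must be positive at entry ("through a qualitative interpretation of the polymerase chain reaction technique", Table 1), so counting that result would leave nobody to exclude. Primary endpoints ties efficacy to each arm's end of treatment, and the Discussion speaks of detection after treatment as failure. The sensible reading is a positive result after treatment.

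It also stands that 25% v 5% is a severe assumption, and that at modest losses the effect is a point or two.

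**Conclusion.** The concern holds in a limited form. As written, membership of the per-protocol set depends on the outcome for patients lost to follow-up. The failure rate in each arm exceeds the completers' rate by construction, and exceeds the true rate if loss is unrelated to response. The bias is larger in the arm with more losses when failure rates, and the chance of seeing a failure before loss, are similar across arms.

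Under the stated assumptions (30% true failure, non-informative loss, half to four fifths of lost patients' failures seen), the size is about 1 to 2 points at 10% lost and 2.5 to 4 points at 20%. It is under 1 point at 5%. Inflated rejection is noticeable only with strongly unequal losses. The loss rates are assumptions; the article gives none.

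This is a flaw in a supplementary analysis. It does not touch the primary intention-to-treat result or the sample size of 240. It merits correction because the rule is explicit, nothing else in the article repairs it, and the repair is simple.

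**What to change.** Define the per-protocol set without reference to the PCR result, and replace the sentence on losses with one of these:

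1. All patients lost to follow-up are excluded from the per-protocol proportion, whatever their PCR results; or
2. All patients lost to follow-up who otherwise qualify are kept, and the 12-month failure probability per arm is estimated by the Kaplan-Meier method already planned, with censoring at the last PCR for those not yet positive.

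In a visit-based simulation with true failure of 30%, 25% lost and loss unrelated to response, both options returned 30.0%, against 33.4% under the present rule. That result depends on loss being non-informative. In either case, report the number lost per arm.

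The cost is one sentence and no new data. Option 1 is simpler but discards some observed failures. Option 2 uses all observed PCR results but replaces the raw proportion with a Kaplan-Meier estimate and assumes non-informative censoring.
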